### Patient and public involvement

A workgroup was organised with the Wessex Subarachnoid Haemorrhage Support Group to discuss UIA research where it was confirmed that better decision making on aneurysm treatment is the main concern for patients, but patients do not want to have their management randomised and therefore an RCT is unlikely to succeed. Consequently, a better understanding of the natural history of UIA was deemed the top priority and that long-term, ideally lifetime risks, are what is relevant to patients. This formed the basis of the current study.

During May 2020, while face-to-face public involvement was not possible due to the COVID-19 pandemic, patients in the neurovascular telephone clinic at University Hospital Southampton were surveyed to assess the study design. All patients strongly supported a study of the natural history of UIA. Although some said they would decline participation in imaging or interventional studies, all confirmed they would be happy for their records to be searched for a natural history study, without full informed consent as is proposed.

## Ethics and dissemination

### Ethical considerations (including informed consent)

Seeking informed consent from all patients to break confidentiality and transfer their identifiable details is not possible without biasing the results. Patients whose aneurysm ruptures have a high likelihood of death or severe disability which would leave them unable to provide informed consent. If informed consent was mandatory, the final cohort would contain an under-representation of patients whose aneurysm ruptured, thus skewing the observed rupture rates.

In order to process patient identifiable data without consent, the study has been given conditional support under Section 251 from the HRA Confidentiality Advisory Group (21/CAG/0033). This allows the transfer of patient identifiable data outside of the direct clinical care team for the purpose of this study. The patient identifiable data can thus be transferred to the coordinating team who in turn can upload these data to the HES/PEDW/SMD databases. The protocol has also been reviewed by the South Central Hampshire A Research Ethics Committee (REC) and issued a favourable opinion in March 2021 (21/SC/0064). The REC and CAG committees will be updated on all significant protocol amendments by the study coordinator.

### Monitoring

As a study without direct patient contact there will not be a separate data monitoring committee. Instead, this role will be conducted by the trial management committee.

### Dissemination and data availability

The results will be disseminated in peer-reviewed journals. Authorship will follow International Committee of Medical Journal Editors recommendations and professional writers will not be used. On completion of the study, the anonymised dataset will be available both to members of the ROAR collaboration and other external researchers. They will be available from the chief investigator on reasonable request.

## Discussion

Although the natural history of UIA has been previously investigated with multiple prospective cohort studies, the rupture rate has varied significantly between these. The design of the ROAR study addresses many of the criticisms of these previous natural history studies. ISUIA^7^ is the first natural history study and is drawn from a population that is genetically closest to that of the UK. However, its results are subject to selection bias with 71% of their UIA being treated either before inclusion or during follow-up. It is not known if that selection was random or based on a feature associated with risk such as aneurysm irregularity. It is therefore not known how the rupture rates in the remaining potentially lower-risk patients translate to the general population. The UK has a much lower treatment rate of UIA (approximately 20%). This is one of the lowest rates in a high-income country making it the ideal setting for a natural history study. It remains however that there will be some treatments performed during the study which inevitably will produce some selection bias that cannot be eliminated. Other countries with lower treatment rates are likely to also have low availability of imaging and hence much lower case identification limiting the cohort size and introducing different biases.

There is also a risk of selection bias in ROAR arising from the methods employed for patient identification. Patients in whom no MDT, clinic notes or radiology report was created would be effectively excluded. These are also the patients more likely to not undergo treatment. However, our survey of UK neurovascular surgeons suggest it is only a very small minority that are not discussed at MDT or seen in a neurosciences clinic. This was also borne out in pilot studies in the development of the protocol. The timeframe for searching patients within a unit’s available records creates the potential for introducing prevalence-incidence selection bias. The ROAR study will mitigate this by identifying patients as *new* or *follow-up* based on whether or not the UIA was diagnosed during that unit’s search window and use the identifying document dates accordingly.

The largest UIA studies are based on Japanese populations and the study with the least bias on a Finnish population. Both observed higher rates of aneurysm rupture than ISUIA. Although it has been assumed ethnicity is a risk factor for rupture and therefore included in the PHASES score, it is not known if the different rupture rates in these studies were due to differences in genetics, environment or study design (and consequently biases). The ROAR study will observe rupture rates in a UK population which removes any concerns over the influence of ethnicity in the results and makes it generalisable for UIA decision making in patients in the UK. Given the use of national-level databases, ROAR is designed as a single country study and as a result there are limitations to its generalisability outside the UK. However, the UK’s population probably more closely resembles most European and North American countries than Japan or Finland.

With the exception of the study by Juvela *et al*,^9^ the follow-up lengths of previous UIA natural history studies are <5 years. Patients are generally not interested in such short-term risks and want to know their lifetime risk. Unfortunately, it is not known if risk is constant over time and therefore if these short-term estimates can be extrapolated to a patient’s lifetime. The hybrid design of the ROAR study will immediately generate follow-up periods of up to 15 years per patient. These will still be shorter than the typical 30-year life expectancy of someone diagnosed with a UIA at 50 and there will still therefore be limitations to extrapolation. However, it will be possible to perform repeat searches of the prospectively maintained databases for hospital admissions and deaths at intervals in the future such that ultimately it will yield realistic lifetime estimates.

Long-term follow-up of such a large cohort of patients is only feasible through the use of national databases. A traditional prospective study would be too costly and time consuming to be realistic as well as suffering significant loss to follow-up. The risk posed by using national databases is that patients emigrating are not censored when they leave the country. However, these databases record when patients deregister their general practice at which time they will be censored from further analysis.

One of the limitations of using national databases for hospital admissions is that identifying rupture events relies on the accuracy of the hospital coders and the diagnosis codes they assign (both to the primary and secondary diagnoses). The ROAR study will assess the magnitude of any miscoding by collecting any available follow-up data from the neurosciences record. In cases where a confirmed aneurysm rupture occurred, we will examine which hospital codes were assigned to that episode. We will also mitigate this limitation by searching for codes for all types of intra-cranial haemorrhage, not just subarachnoid haemorrhage, and subsequently review the medical records and imaging studies to confirm the true diagnosis for that patient.

While subject to a number of limitations, the ROAR study has mitigations for most of these and will therefore be less susceptible to them than previous studies. It is therefore expected to definitively evaluate the validity of PHASES, assess additional predictors of rupture and assess long term risks of rupture.

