Patient identifiable details (name, date of birth, post code, NHS/CHI number) will be securely sent by each neurosurgery unit to the coordinating centre for consolidation and linkage to the national databases for hospital admissions. These databases are: Hospital Episode Statistics (HES), Patient Episode Database for Wales (PEDW) and Scottish Morbidity Database (SMD). These databases also link to the Civil Registrations—Death and National Registry Scotland for death records. Patients will be linked to hospital admissions based on International Classification of Diseases 10th Revision (ICD-10) diagnosis codes for intracranial haemorrhages and OPCS4 codes for aneurysm occlusion treatments. These databases record every hospital admission in their respective country and thus using this as the outcome source, combined with death records, will allow identification of every aneurysmal subarachnoid haemorrhage (aSAH) regardless of whether they were managed in a neurosurgery unit, a district general hospital, migrated out of the region in which their UIA was diagnosed, or died in the community. The number of patients with aSAH who are not captured by this method, either because they do not present to hospital or emigrate out of the UK, is expected to be very small. Rupture rates can be adjusted based on national emigration rates.

Patients will be censored if there is any occlusive treatment of the UIA or patient death. Occlusive treatment includes either microsurgical or endovascular techniques either partial or complete. If none of these censoring events are observed, then they will be censored on the day the cohort is submitted to the HES/PEDW/SMD databases.

The ICD-10 codes to be searched for rupture events have been selected in accordance with the UK Biobank stroke research and include: aSAH (I60.1-9), intracerebral haemorrhage (I61.0-9), traumatic subarachnoid haemorrhage (S06.6) and spontaneous subdural haemorrhage (I62.00-I62.02).^16^ The use of codes beyond those for aSAH will capture any hospital admissions for aneurysm rupture which have resulted in other forms of intracranial bleed or have been miscoded.

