### Statistical analysis

#### Objective 1: PHASES validation

The PHASES study provides the coefficients from their Cox regression model and baseline survival at 5 years which allows the absolute 5-year risk of rupture to be calculated for all patients who are not censored before 5 years. Time to censoring will be calculated (whichever is soonest of the date of treatment, date of death or the HES/PEDW/SMD search date) to ensure 5 years of follow-up if rupture has not occurred. Discrimination will be assessed using Harrell’s C-index of concordance and Royston and Sauerbrei’s D statistic. Calibration will be assessed at the 5-year time point using the method by Royston.^19^ These will be used to calculate the number of SAH events per 5 years for each PHASES score (≤2 to 12+) and expressed as a percentage with 95% CI to compare with the PHASES estimates.

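### The censoring lists in Study design and Objective 1 omit the censoring at GP deregistration that the Discussion promises for emigrants (minor)

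*Protocol article*

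**What the plan says.** The protocol article deals with the end of follow-up in three places.

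- **Study design** gives the rule: "Patients will be censored if there is any occlusive treatment of the UIA or patient death". It then closes the list: "If none of these censoring events are observed, then they will be censored on the day the cohort is submitted to the HES/PEDW/SMD databases".
- **Objective 1: PHASES validation** repeats it for the 5-year analysis, taking "whichever is soonest of the date of treatment, date of death or the HES/PEDW/SMD search date".
- **Discussion** raises emigration as a weakness: "The risk posed by using national databases is that patients emigrating are not censored when they leave the country". The sentence that follows gives the remedy: "these databases record when patients deregister their general practice at which time they will be censored from further analysis".

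Study design has its own answer to emigration, at the level of rates and not of individuals: "Rupture rates can be adjusted based on national emigration rates". It expects few events to be missed through emigration but gives no figure. The same section counts it as a strength that ruptures are found in patients who have "migrated out of the region in which their UIA was diagnosed".

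**The concern.** The two lists in the methods are closed. If neither treatment nor death is observed, the patient runs to the submission date, which leaves no room for an earlier end at deregistration. The Discussion says that such patients will be censored earlier. An analyst who works from the methods and one who works from the Discussion would give the same emigrant different follow-up times.

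The choice matters because a patient abroad cannot contribute a rupture to UK admissions data. Nor would treatment abroad appear there, and a death abroad may not reach UK death records. If such patients are kept to the search date they add person-time without events. Because nothing removes them, they become a growing share of the late risk set. Objective 3 asks about risk beyond 5 years and uses a cumulative hazard plot to judge whether risk is constant, so a late hazard diluted in this way could be mistaken for a real decline.

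The optional adjustment by national emigration rates adds a second difficulty: applied on top of individual censoring, it would correct the same problem twice.

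**Working it through.** **Text comparison.** Take a living, untreated patient who leaves the UK and deregisters in year 6, with the search in year 12.

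| Place | End of follow-up |
|---|---|
| Study design | submission date, year 12 |
| Objective 1 | search date, year 12 (cut at 5 years for this objective) |
| Discussion | deregistration, year 6 |

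Study design and Objective 1 agree, since submission date and search date are in substance the same administrative date. There are thus two rules, and they cannot both be applied to this patient.

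**Size.** The plan states no figure to reproduce here, so the effect is shown over a range.

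Input from the document:
- Rupture rate from the ISUIA figures under Sample size: 51 / (1692 × 4.1) = 0.00735 per year.

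Assumptions:
- Entry uniform over 2006 to 2020 (the maximum search window) and search on 31 July 2023 (the planned end of baseline collection), so potential follow-up *f* is about 2.6 to 17.6 years.
- Treatment 2% and death 2% per year. Constant rates throughout.
- Emigration *e* = 0.1%, 0.25% or 0.5% per year.
- Rupture, treatment and death abroad are all unseen.

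Let k = 0.00735 + 0.02 + 0.02 = 0.04735.

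*Share of the nominal risk set abroad at time t.* Still in the UK and at risk: U(t) = exp(−(k+e)t). Abroad but counted at risk: A(t) = e/(k+e) × [1 − exp(−(k+e)t)]. Share = A/(A+U).

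For e = 0.005 and t = 15: U = exp(−0.05235 × 15) = 0.456; A = 0.005/0.05235 × 0.544 = 0.052; share = 0.052/0.508 = 10.2%.

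*Relative understatement of the rate.* This equals the fraction of counted person-time spent abroad. Observable time up to *f* is H(f) = [1 − exp(−(k+e)f)]/(k+e), and time abroad is B(f) = e/(k+e) × [f − H(f)]. Average each over the distribution of *f* and take B/(B+H).

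For e = 0.005: mean H = 7.541 years, mean B = 0.2425 years; 0.2425/7.783 = 3.1%. With *f* fixed at 5 years: H = 4.399, B = 0.0574; 0.0574/4.457 = 1.3%.

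| Assumed emigration per year | Overall rate understated by | First 5 years only | Abroad among those counted at risk at 15 years |
|---|---|---|---|
| 0.1% | 0.6% | 0.3% | 2.2% |
| 0.25% | 1.6% | 0.6% | 5.3% |
| 0.5% | 3.1% | 1.3% | 10.2% |

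In absolute terms, at 0.5% emigration a true 0.735% per year would be observed as 0.735 × (1 − 0.031) = 0.712%. The hazard at 15 years is understated by the share in the last column, because that fraction of the denominator cannot yield an observed event.

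*Double correction.* If emigrants are already censored and the rate is then scaled up for emigration as well, the result is too high by about 1/(1 − 0.031) − 1 = 3.2% at 0.5% emigration, so the bias changes sign and is not removed.

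**The case against.** The strongest reply is that the problem has been seen and largely answered. The Discussion recognises emigration and commits to individual censoring, which is close to the right remedy. The article condenses a fuller protocol, which may carry the registration field and the exact rule. The effect on 5-year results is about 1% or less for most of the range, in line with the article's expectation that few events are missed. All of this stands, and it is why the point is minor. It does not remove the conflict: the article states both rules, and the one in the methods excludes the one in the Discussion.

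Two stronger readings are tempting, and the document supports neither.

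- *Three conflicting definitions of time at risk.* Study design and Objective 1 state the same rule. The emigration-rate adjustment corrects a rate and does not define follow-up. It is also permissive, and nowhere does the article say that it will be combined with individual censoring. Double correction is a risk to be closed off, not a stated plan.
- *Loss of everyone who changes practice.* Read alone, the Discussion's trigger would cover a patient who moves house within the UK and joins a new practice. That would discard follow-up in people whose events Study design says are still captured after they have "migrated out of the region in which their UIA was diagnosed". But the preceding sentence in the Discussion is about leaving the country, and the Study design sentence concerns finding events, not ending follow-up. In context the rule concerns emigration. Any estimate of person-time lost to practice changes therefore rests on a rule that the article does not propose. What is left is a wording point: the Discussion should say that such a move does not count.

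**Conclusion.** The point holds as an inconsistency to reconcile. The censoring lists in Study design and Objective 1 leave out an event that the Discussion says will be applied, and an optional rate adjustment for the same problem stands beside it.

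Following the methods lists would bias rupture rates downward. On the assumptions above the bias is small for Objective 1. It is potentially visible in the tail for Objective 3, where up to about a tenth of the nominal risk set at 15 years could be unobservable. The repeat searches planned about every 5 years would lengthen follow-up and enlarge it. The result scales almost in proportion to the emigration rate, which the documents do not give; at 0.1% per year the effect is negligible for most purposes. Severity: minor.

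**What to change.** Use one rule in Study design, Objective 1 and the Discussion: follow-up ends at the earliest of occlusive treatment, death, end of UK general practice registration without re-registration anywhere in the UK, or the search date.

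Then:
- State that a change of practice within the UK is not a censoring event.
- Obtain the registration-end date for every submitted patient, not only for those with a matched admission or death. The linkage in Study design is described through haemorrhage codes, treatment codes and death records, and does not mention registration dates.
- Keep the adjustment by national emigration rates only as a sensitivity analysis, or where registration dates cannot be obtained, and say that it is not applied on top of individual censoring.

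The cost is a few sentences and one extra field in the linkage request. The downside is slightly fewer patient-years than under the methods lists, by the overall percentages in the table, all of it time in which a rupture could not have been seen.

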## Data Availability

Data are available on reasonable request.
